# A protocol for a multicentre, parallel-group, pragmatic randomised controlled trial to evaluate the NEVERMIND system in preventing and treating depression in patients with severe somatic conditions

**DOI:** 10.1186/s12888-020-02494-3

**Published:** 2020-03-02

**Keywords:** Depression, RCT, Prevention, Treatment, eHealth, Intervention, Evaluation, Somatic condition, Quality of life, Patients, Nevermind, Horizon 2020

## Abstract

**Background:**

Depressive symptoms are common in individuals suffering from severe somatic conditions. There is a lack of interventions and evidence-based interventions aiming to reduce depressive symptoms in patients with severe somatic conditions. The aim of the NEVERMIND project is to address these issues and provide evidence by testing the NEVERMIND system, designed to reduce and prevent depressive symptoms in comparison to treatment as usual.

**Methods:**

The NEVERMIND study is a parallel-groups, pragmatic randomised controlled trial to assess the effectiveness of the NEVERMIND system in reducing depressive symptoms among individuals with severe somatic conditions. The NEVERMIND system comprises a smart shirt and a user interface, in the form of a mobile application. The system is a real-time decision support system, aiming to predict the severity and onset of depressive symptoms by modelling the well-being condition of patients based on physiological data, body movement, and the recurrence of social interactions. The study includes 330 patients who have a diagnosis of myocardial infarction, breast cancer, prostate cancer, kidney failure, or lower limb amputation. Participants are randomised in blocks of ten to either the NEVERMIND intervention or treatment as usual as the control group. Clinical interviews and structured questionnaires are administered at baseline, at 12 weeks, and 24 weeks to assess whether the NEVERMIND system is superior to treatment as usual. The endpoint of primary interest is Beck Depression Inventory II (BDI-II) at 12 weeks defined as (i) the severity of depressive symptoms as measured by the BDI-II. Secondary outcomes include prevention of the onset of depressive symptoms, changes in quality of life, perceived stigma, and self-efficacy.

**Discussion:**

There is a lack of evidence-based interventions aiming to reduce and prevent depressive symptoms in patients with severe somatic conditions. If the NEVERMIND system is effective, it will provide healthcare systems with a novel and innovative method to attend to depressive symptoms in patients with severe somatic conditions.

**Trial registration:**

DRKS00013391. Registered 23 November 2017.

## Background

Depressive disorders are one of the leading causes of the burden of disease globally. It is the third leading cause of disability worldwide [1] with an estimated one-year prevalence of depression of approximately 3% in the general population [2]. This increases significantly in individuals with severe somatic conditions as there is a high likelihood of developing a comorbid mental illness. The prevalence of depressive symptoms in patients who have suffered acute myocardial infarction (MI) is estimated at 14% [3] while the prevalence in individuals with chronic kidney disease can range between 26 and 39% [4]. Depressive symptoms are defined as symptoms experienced by patients as identified with self-reported or rater-based scales. Depression, as confirmed with a clinical diagnosis and/or identified with ICD codes, in patients with chronic kidney disease has a prevalence that ranges between 21 and 22.8% [4], and between 3 and 28% in cancer patients depending on the cancer type and treatment phase [5]. However, in reality, these estimates are likely to be higher as depression is often under-reported and under-detected [6]. Moreover, these estimates do not account for other comorbidities, which have been shown to increase the risk of depression. A review of the literature on chronic conditions and comorbid depression found 1.7 increased odds of depression in patients with more than one chronic illness compared to patients with only one chronic illness [7].

This added burden of disease increases the strain felt by the patient, impacting the outcome of the primary disease [8] as well as quality of life (QoL) [2], and thereby can result in a reduction in the management of symptoms [6]. A meta-analysis assessing the impact of depression on mortality after MI indicated that patients who develop depression after MI are at a 13% increased risk of subsequent cardiac events and 22% increased risk of all-cause mortality [9]. In addition to the burden on the patient, there is an added burden on the healthcare system. It has been estimated that cancer patients with comorbid depression have a 32% higher healthcare expenditures and are more likely to use emergency care compared to patients who do not have comorbid depression [10].

Research has shown that while this double burden of disease is common in patients with severe somatic conditions, little is done to prevent the progression of depression and other mental disorders. The standard general practitioner’s guidelines for patients diagnosed with any severe somatic condition are to provide information to patients about improving diet, physical activity, and psychological well-being [11] to prevent subsequent illnesses. However, patients often do not adhere to these guidelines [12]. Moreover, severe somatic conditions generally require considerable lifestyle changes and without proper guidance, this can be very difficult for the patient, especially with concurrent depressive symptoms. Currently, in most European Union (EU) healthcare systems, treatment for patients with serious somatic conditions does not incorporate any preventive methods or early diagnosis of the onset of comorbid depressive symptoms.

The NEVERMIND system, which stands for NEurobehavioural predictiVE and peRsonalised Modelling of depressIve symptoms duriNg primary somatic Conditions with ICT-enabled self-management procedures, aims to fill this gap and give patients more control over their mental and physical wellbeing. The NEVERMIND project comprises a research consortium of nine different centres in six countries that include *Spain*, *Sweden*, *Germany*, *Portugal*, *United Kingdom* and the coordination centre in *Italy*. The feasibility of the NEVERMIND project is based on a previously funded EU project, PSYCHE, where a multiparametric monitoring system based on a sensorised shirt and a smartphone was used to gather physiological and behavioural data of patients affected by mood disorders [13, 14]. The NEVERMIND system collects physiological data and psychometric data to assess the risk of developing depressive symptoms. It also contains interactive online cognitive-behavioural therapy (CBT) modules, which are offered to patients based on their symptoms of depression. It is anticipated that the NEVERMIND system will encourage patients to become more self-reliant, engage more in self-care behaviours, use CBT techniques, and increase their confidence in their ability to carry out daily life activities. All these factors should combine and contribute to a new self-image of a patient and aid in reducing depressive symptoms as well as improving the overall quality of life for the patient.

## Objectives

The primary objective is to assess the effectiveness of the NEVERMIND system in reducing depressive symptoms in patients with a somatic condition in comparison to treatment as usual (TAU). Secondary objectives are the effectiveness of the NEVERMIND system in preventing new symptoms of depression, improving quality of life, perceived stigma, and self-efficacy.

## Methods

### Trial design

The study is a multicentre randomised (1:1) control, parallel-group pragmatic trial conducted in Italy and Portugal that will assess the effectiveness of the NEVERMIND system compared to TAU. Patients will be recruited at three clinical centres; Pisa and Turin in Italy and Lisbon in Portugal. It is hypothesised that the NEVERMIND system is superior to TAU. The study will be conducted according to the CONSORT guidelines for randomised controlled parallel, non-pharmacologic trials [15, 16]. The study design is illustrated in Table 1.

**Table 1 Tab1:**
[figure not shown]
Flow diagram of the study design

Enrolment including eligibility screening and randomisation into either the intervention or control group took place since November 2017, and enrolment will end in December 2019. Baseline assessments were conducted after randomisation and 12-week post-intervention and 24-week post intervention assessments were conducted. The study is planned to end in March 2020.

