#### Exclusion criteria

Patients are excluded if they have a past diagnosis of a major psychiatric disorder other than depression. These psychiatric disorders include bipolar disorder, psychosis, and suicidality. Therefore, a diagnosis of depression as a disorder or depressive symptoms is not an exclusion criterion. Moreover, patients are excluded if they have had any recent and active severe suicidality as assessed by the Paykel Suicide Scale [17] or if they have been in treatment with a stable drug therapy for less than two months. Patients are also excluded if they have any cognitive impairment, such as dementia. Moreover, individuals are excluded if they have been involved in other structured psychological treatments involving mindfulness, CBT, other relaxation techniques, or other structured psychotherapy within the three months preceding enrolment. An individual is also ineligible if they have participated or are currently participating in any clinical trial including but not limited to pharmacological trials that might interfere with the study objectives. A lack of capability to participate in study procedures including giving consent will also result in ineligibility. Finally, individuals are ineligible if they demonstrate an inability to use Smartphone technology, especially touch screen interaction and basic maintenance procedures of the devices (e.g. includes charging, switching on and off, reading notifications, making calls, and sending and receiving text messages). Patients’ ability to use Smartphone technology was assessed by asking patients whether they are able to use smartphones to check and send emails.

All patients that meet the inclusion criteria are asked to participate after a comprehensive explanation of the study. Patients provide written consent following the guidelines set by the local ethics committee. Once the patients have consented, they are randomised to either the intervention group or the control group. Subsequently, they are asked to complete the baseline questionnaire. The primary outcome is assessed at 12-weeks after baseline assessment, and a follow-up assessment occurs at 24 -weeks.

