### Randomisation

#### Sequence generation & allocation concealment

Participants are randomly assigned following randomisation procedures to either the intervention group or the control group. Block randomisation is used to ensure an equal number of patients in the intervention and control group at each site. The block randomisation randomizes patients in the control and treatment group in blocks of size ten. This is necessary as each clinical centre treats different somatic conditions, and these should be equally distributed between the two groups. Randomisation is centralized and carried out by an electronic system developed by UPM (Universidad Politécnica de Madrid) in collaboration with KI (Karolinska Institutet). This is done to conceal the randomisation from the researchers involved in enrolment and assessment.

Once the patient has met the eligibility criteria and is enrolled in the study, he/she will complete the baseline assessment. The clinician will then connect to a web page and obtain a randomly generated code to be assigned to the patient. The patient will be assigned to either the control group or the intervention group according to the code.

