#### Blinding

Blinding of patients and treating physicians to treatment allocation is not possible. The clinical psychologists who evaluate the patients at baseline and the two follow-up assessments are, however, different from those who randomise and allocate the patients to either the intervention or control group as well as provide the intervention group about the NEVERMIND system. All evaluators are blinded to the group allocation. Any incidence of unblinding is reported to and recorded by the respective centres.

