#### Statistical analysis

Intention-to-treat (ITT) analysis will be carried out, which hypothesises the superiority of the NEVERMIND system in reducing depressive symptoms in comparison to TAU. A linear mixed model will be used in order to use all available data of each subject and choose an appropriate covariance structure reflecting the potential dependence due to repeated measures. In order to account for the repeated measurements, the baseline measures will be adjusted for in the model [30, 34]. This increases statistical power, accounts for regression towards the mean, and has been recommended for longitudinal analysis of RCTs [35, 36]. Therefore, the ITT for the primary outcome (BDI-II score at 12-weeks) will be used as recommended for statistical analysis of clinical trials by the European Medicines Agency (EMA; codes CPMP/ ICH/363/96 and CPMP/EWP/2863/99). Group (intervention and control), disease type, and hospital will be included as fixed factors.

Comparison of demographic and clinical characteristics at baseline between subjects of varying primary somatic conditions and clusters as well as between intervention and control group will be examined. In case of imbalances of some characteristics, explorative sub-group analyses will be performed.

If a difference between ITT and per-protocol analysis is observed, more weight will be given to the ITT analysis, which is seen as the primary analysis. If the NEVERMIND system does not show superiority effect over treatment as usual for the ITT analysis, we will look at the extent of usage of the different components of the NEVERMIND system. Additionally, secondary analyses of the primary outcome will include per-protocol evaluations and examine the preventive effect of the NEVERMIND system on the incidence of depression (sensitivity analysis). Analyses of the other secondary outcomes (quality of life, perceived stigma and self-efficacy) will be examined in a similar manner.

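### The protocol article places the baseline assessment both after and before randomisation; if it came after, the covariate in the primary model may have been affected by allocation

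*Protocol article*

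**What the plan says.** Three places in the protocol article fix the order of baseline and randomisation, and they do not agree.

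- **Trial design, text under Table 1:** "Baseline assessments were conducted after randomisation and 12-week post-intervention and 24-week post intervention assessments were conducted". Baseline comes second, in the past tense.
- **Exclusion criteria, last paragraph:** "Once the patients have consented, they are randomised to either the intervention group or the control group", and then "Subsequently, they are asked to complete the baseline questionnaire". Baseline again comes second.
- **Sequence generation & allocation concealment:** "Once the patient has met the eligibility criteria and is enrolled in the study, he/she will complete the baseline assessment", and then "The clinician will then connect to a web page and obtain a randomly generated code to be assigned to the patient". Here baseline comes first.

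Three further statements determine what hangs on this order. Blinding states: "Blinding of patients and treating physicians to treatment allocation is not possible"; only the evaluators are blinded. Evaluation procedures says that data are collected with self-report questionnaires at baseline, 12 and 24 weeks. Statistical analysis says of the primary linear mixed model that "the baseline measures will be adjusted for in the model", giving power and regression towards the mean among the reasons. The primary outcome is BDI-II 12 weeks after the baseline assessment.

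**The concern.** Adjusting for a baseline value is safe when treatment allocation cannot have influenced it. A value recorded before the allocation code exists meets that condition by design. A questionnaire completed by a patient who already knows the arm need not: being given the new system, or being told of usual care only, can move a depression self-rating on that day. Part of the adjustment then removes or adds a difference that allocation itself created, and the arguments offered for adjusting no longer apply cleanly. Evaluator blinding does not protect what an unblinded patient writes on a form.

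The secondary question of preventing new depressive symptoms is exposed in the same way, because it depends on who had symptoms at baseline. As the text stands, a reader cannot tell whether the covariate in the primary analysis is a pre-randomisation measure.

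**Working it through.** **The plan's own figure.** With d = 0.54, 80% power and a significance level of 0.05 (taken as two-sided), the normal approximation gives n per arm = 2 × (1.960 + 0.842)² / 0.54² = 53.8, so 54 per arm and 108 in total. A two-sample t-test gives 54.8, so 55 per arm and 110 in total, which is the stated figure. Dividing by the assumed one-third with symptoms gives 110 × 3 = 330. The sample size reproduces, and the order of baseline and randomisation does not change it.

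**Inputs for the bias.**

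- Planned effect: d = 0.54 (Sample size).
- Slope of 12-week BDI-II on baseline, in SD units: 0.5. This reads the intercorrelation coefficient in Sample size as the baseline-to-12-week correlation, which is an interpretation.
- Shift *s* in one arm's mean baseline caused by knowing the arm: not in the article. Assumed 0.1 to 0.3 SD, and transient, so that it does not carry over to week 12.

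**Formula.** Adjusted effect = (12-week difference) − slope × (baseline difference), both taken as intervention minus control. Bias in size = slope × *s*. This treats the 12-week contrast of the mixed model as an analysis of covariance.

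| Shift *s* | Bias | Share of 0.54 |
|---|---|---|
| 0.1 SD | 0.5 × 0.1 = 0.05 SD | 0.05 / 0.54 = 9% |
| 0.2 SD | 0.5 × 0.2 = 0.10 SD | 0.10 / 0.54 = 19% |
| 0.3 SD | 0.5 × 0.3 = 0.15 SD | 0.15 / 0.54 = 28% |

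With *s* held at 0.2 SD and the slope varied from 0.3 to 0.7, the bias is 0.06 to 0.14 SD. A simulation at slope 0.5, *s* = 0.2 and 330 patients returned a bias of 0.100 SD in size.

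**Direction.** Lower BDI-II is better. Hope lowers baseline scores in the intervention arm; disappointment raises them in the control arm. Both make the baseline difference negative, say −0.2. The adjusted effect then becomes the 12-week difference − 0.5 × (−0.2), that is, the 12-week difference + 0.10, which moves it towards no benefit. A positive baseline difference does the reverse. What matters is the sign of the difference, not which arm moved.

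**Effect on the test.** With no true effect, SE = √(1 − 0.5²) × √(4/330) = 0.866 × 0.110 = 0.095. A bias of 0.05, 0.10 or 0.15 SD raises the two-sided rejection rate from 5% to 8.2%, 18.2% or 35.0% (simulation at 0.10: 17.8%). Under hope or disappointment, almost all the excess rejections favour usual care.

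**The case against.** The strongest reply is that the problem is conditional. If the order in Sequence generation & allocation concealment was followed, the covariate is a proper pre-randomisation measure and only wording needs correcting. Nor does the article say that patients had been told their arm when they completed baseline; it says that blinding them is not possible. Its mixed list of rater-based and self-report scales does not label BDI-II individually as self-report. And the mechanisms that come first to mind would work against the intervention, so they threaten power more than they threaten a false claim of benefit. All of this stands, and it limits the finding to a contradiction with a conditional consequence. It does not remove the contradiction: two places state one order, one states the other, and the article offers no way to choose.

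A reader might go further and infer that eligibility was also settled after allocation, because patients are excluded for "recent and active severe suicidality as assessed by the Paykel Suicide Scale" and that scale is in the baseline battery. The text does not support this. Trial design puts eligibility screening within enrolment, alongside randomisation; Exclusion criteria seeks consent from patients who meet the criteria and only then randomises them; and Sequence generation & allocation concealment starts from patients who have already met the criteria. Use of the scale in the battery does not show that it was absent from screening.

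It is also fair to say that including patients without a baseline will add few to the 12-week comparison. Week 12 is counted from the baseline assessment, and the article rules out imputing the primary outcome at that time.

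**Conclusion.** The article contradicts itself on whether baseline preceded randomisation, and the primary model uses that baseline. This needs correcting as written. If baseline followed allocation and patients knew their arm, the adjusted 12-week effect is biased by about slope × the baseline difference that allocation induced: 0.05 to 0.15 SD, or 9% to 28% of d = 0.54, for an assumed shift of 0.1 to 0.3 SD and an assumed slope of 0.5. The article supplies neither the shift nor its sign, so these figures show a range of possibilities and estimate nothing about this trial.

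Two stronger inferences should be resisted. The article does not establish that the covariate was in fact post-allocation. And the bias should not be set against a diluted effect of 0.54 / 3 = 0.18, because that assumes no effect at all in patients without baseline symptoms, which the article does not say.

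**What to change.** 1. State the order actually used, and reconcile Trial design, Exclusion criteria and Sequence generation & allocation concealment with it. The sentence under Table 1 reports past conduct, so it should not be rewritten to match the other order unless the records show it to be wrong.
2. For any patients still to be enrolled, complete all baseline scales before the allocation code is obtained, as Sequence generation & allocation concealment already says.
3. For patients already enrolled, compare baseline dates with the randomisation records and report how many baselines followed allocation.
4. If there are any, report the 12-week comparison without baseline BDI-II adjustment beside the adjusted one. Include every randomised patient with a 12-week value, with or without a baseline. State the same caveat for the prevention analysis.

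The cost is a text correction, a record check and one sensitivity analysis. The article does not say whether the electronic system logs the time of baseline completion, so the check may have to use the centres' own records. The unadjusted comparison loses some precision: at a correlation of 0.5 its standard error is 1 / √0.75 = 1.15 times the adjusted one. The target of 330 is unchanged.

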### Outcomes

#### Primary outcome

Hypothesis: NEVERMIND will significantly decrease the level of depressive symptoms in the intervention group in comparison to TAU in the control group;

Outcome measure*:* the severity of depressive symptoms as measured by the Beck Depression Inventory II (BDI-II) at T12 (12-weeks post baseline assessment).

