### Trial status

The trial began enrolment in December 2017. Recruitment will be completed by March 2020. The trial has been registered on 23 November 2017 (DRKS00013391). [https://www.drks.de/drks_web/navigate.do?navigationId=trial.HTML&TRIAL_ID=DRKS00013391].

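### The stated study end of March 2020 leaves no room for the 24-week assessment of patients enrolled up to December 2019

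*Protocol article*

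**What the plan says.** All dates are in the protocol article.

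- **Trial design, text beneath Table 1.** Enrolment "took place since November 2017" and "enrolment will end in December 2019". Then: "The study is planned to end in March 2020". The two follow-up visits are labelled there as 12 and 24 weeks post-intervention.
- **Trial status.** "The trial began enrolment in December 2017" and "Recruitment will be completed by March 2020".
- **Exclusion criteria, last paragraph.** The primary outcome is taken 12 weeks after the baseline assessment, and "a follow-up assessment occurs at 24 -weeks".
- **Primary outcome; Secondary outcomes; Evaluation procedures.** The BDI-II endpoint is at 12 weeks from baseline. Sustainability of the effect is a secondary outcome at 24 weeks from baseline. Data are collected at baseline, 12 weeks and 24 weeks.
- **Statistical analysis.** Week 24 is equated with 12 weeks after the intervention ends. A missing 24-week outcome due to loss to follow-up may be replaced by the 12-week value. Nothing is imputed for the primary outcome at week 12.
- **Participants.** The target is 330 patients, 165 per group.

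**The concern.** From the end of enrolment to the end of the study is at most four calendar months, and the last scheduled assessment is 24 weeks after baseline. No section excuses late enrollees from that visit or says that the study ends at the 12-week visit. If the dates are followed, the latest enrollees have no week-24 data by design.

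What is at stake is the week-24 comparison. It loses precision, and the analysis has to handle values that are missing because the calendar ran out and not because patients left. The plan's missing-data wording addresses loss to follow-up only. If these visits were swept into that category and filled with week-12 scores, the week-24 result for those patients would repeat their week-12 result.

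The article also gives two recruitment starts and two statements about when recruitment ends, so the true length of the gap cannot be read from it.

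**Working it through.** **Inputs.** Enrolment end December 2019 and study end March 2020 (Trial design); recruitment completed by March 2020 (Trial status); start November 2017 (Trial design) or December 2017 (Trial status); visits at 12 and 24 weeks from baseline (Primary outcome, Secondary outcomes); target 330 (Participants). Only months are given, so the first and last day of each were tried. Baseline is taken as the enrolment date.

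**Step 1. Can the plan's own end date be reproduced?** Visit date = enrolment date + 7 × weeks.

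| Enrolled | Week 12 | Week 24 | Weeks left to 31 Mar 2020 |
|---|---|---|---|
| 1 Dec 2019 | 23 Feb 2020 | 17 May 2020 | 17.3 |
| 31 Dec 2019 | 24 Mar 2020 | 16 Jun 2020 | 13.0 |
| 1 Mar 2020 | 24 May 2020 | 16 Aug 2020 | 4.3 |
| 31 Mar 2020 | 23 Jun 2020 | 15 Sep 2020 | 0 |

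March 2020 is not reproduced with 24 weeks of follow-up. Even the most generous pairing (enrolment closing 1 December, study closing 31 March) gives 17.3 weeks. March 2020 does match the last **12-week** visit for December 2019 enrolment (23 February to 24 March 2020).

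**Step 2. Latest enrolment date that still allows each visit.**
- Study end 31 March 2020: minus 24 weeks = 15 October 2019; minus 12 weeks = 7 January 2020.
- Study end 1 March 2020: minus 24 weeks = 15 September 2019; minus 12 weeks = 8 December 2019.

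**Step 3. Size, assuming even accrual.** Patients losing a visit = 330 × (days from the latest workable enrolment date to the enrolment end) / (days of enrolment).

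Enrolment to December 2019, week 24:
- Central illustration (1 Nov 2017 to 31 Dec 2019, study end 31 March): 330 × 77/790 = 32 (10%).
- Smallest (1 Nov 2017 to 1 Dec 2019, study end 31 March): 330 × 47/760 = 20 (6%).
- Largest (31 Dec 2017 to 31 Dec 2019, study end 1 March): 330 × 107/730 = 48 (15%).
- With the study end held at 31 March, the range narrows to 20 to 35.

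Enrolment to December 2019, week 12:
- None lost if the study runs to 31 March. If it closed on 1 March and enrolment ran to 31 December, about 10.

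Recruitment running into March 2020:
- Week 24: 54 to 80 (16 to 24%) over all readings; 54 to 68 with the study end at 31 March.
- Week 12: 21 to 46 (6 to 14%) over all readings; 21 to 34 with the study end at 31 March. The smallest is 330 × 54/851 = 21.
- The upper ends of the all-readings ranges pair recruitment to 31 March with a study end of 1 March, so they are outer bounds.

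**The case against.** **A condensed article need not give every operational date.** True, but the dates here are stated and conflict with one another. This is not an omission.

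**Study end may mean completion of the 12-week phase.** The match in Step 1 makes this a plausible origin for the March 2020 date. No section defines study end that way, and the same paragraph mentions the 24-week assessment.

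**The primary endpoint is not at risk on the dates given.** This stands. A reader might infer from the Trial status section that the 12-week endpoint is cut off too. But completion by March 2020 is only a latest date and is compatible with enrolment closing in December 2019. Under that close, the last 12-week visit is 24 March 2020, inside a study that ends on 31 March.

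**Inflated sustainability is not shown.** This also stands as an unconditional claim. A reader might conclude that carrying week-12 scores forward will exaggerate how long the effect lasts. That needs carry-forward to be applied to these patients and the effect to fade after week 12. The Statistical analysis section is not a clean carry-forward plan: it also names multiple imputation and inverse probability weighting, and lists carry-forward among the sensitivity analyses. It does not say that visits falling after study end count as loss to follow-up. A calendar cut-off should affect both arms of a 1:1 block-randomised trial about equally, so the direct effect is lost precision.

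**The denominator is uncertain.** The Sample size section treats 330 as completers and says that recruitment allows for 20% drop-out, so the number enrolled may be larger. The percentages then still apply, but the counts would be higher.

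**Conclusion.** The stated enrolment end and study end cannot both hold alongside a 24-week assessment of every patient. This is true on every day-of-month reading and needs no assumption about accrual. The number affected does: under even accrual of 330, about 20 to 48 patients (6 to 15%) lose the week-24 visit. Slower or faster accrual in late 2019 would change that.

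The damage on the Trial design dates is confined to a secondary time point, and the primary comparison is intact if the study runs to 31 March 2020. Loss of week-12 data is conditional on recruitment actually continuing past about 7 January 2020.

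The November versus December 2017 start is a plain inconsistency. The post-intervention visit labels beneath Table 1 would, read literally, put the visits at weeks 24 and 36 of a schedule with a 12-week intervention. The outcome sections count from baseline and settle the matter, so this is a minor wording slip.

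The plan is wrong as written and cheap to correct.

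**What to change.** 1. Define study end as the 24-week visit of the last randomised patient. That is mid-May to mid-June 2020 if enrolment closes in December 2019, or mid-August to mid-September 2020 if it closes in March 2020.
2. Give one recruitment start and one recruitment end, the same under Trial design and Trial status.
3. Count all visits from baseline, including in the text beneath Table 1.
4. If the end date cannot move, classify unreached week-24 visits as administratively missing, let the mixed model use the data that exist, and do not fill them with week-12 scores. Carry-forward would overstate sustainability if the effect fades after week 12. Report the number affected by arm.

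Closing enrolment by 15 October 2019 would also have resolved the conflict, but the article is dated 2 March 2020, so that option had passed.

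The cost is a few months of added follow-up for the last patients and a correction of dates. No patients are added.
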